### Hypothesis

Null hypothesis: There is no difference in KOOS QoL following AM or AD treatment of a symptomatic full thickness knee cartilage defect less than 2 cm^2^ 24 months after surgery.

Alternative hypothesis: There is a difference in KOOS QoL following AM or AD treatment of a symptomatic full thickness knee cartilage defect less than 2 cm^2^ 24 months after surgery.

### Statistical analysis

Demographic variables will be presented as mean ± standard deviation (SD) for continuous variables, and frequencies for categorical variables. The normal distribution of the variables will be tested. Given normal distribution, the statistical analysis will be performed using linear mixed models (LMM), including a random center effect for hospital. The test for the primary objective of comparing KOOS QoL from baseline to 24 months between the groups can be performed as a post hoc *t*-test following the LMM. If the data is not normally distributed, a non-parametric analysis will be done using the Mann-Whitney *U*-test. To evaluate the efficacy of treatment in terms of categorical outcome measures we plan to use Chi-squared tests. To adjust for possible confounders such as age of the patient and severity of the cartilage lesion, these variables will be included in the LMM. A *p* < 0,05 is considered statistically significant. The statistical analysis will be conducted in collaboration with a statistician at Unit for Applied Clinical Research at Norwegian University of Science and Technology, using SPSS v.22 (SPSS Inc, Chicago, Illinois) and R [49].

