### Endpoints

The Knee Injury and Osteoarthritis Outcome Score (KOOS) knee-related quality of life (QoL) subscore is the primary endpoint. Validated to use in cartilage research studies, KOOS is a patient reported outcome measure [47], and will enable comparison of our results with other knee cartilage studies. At 24 months follow up, the difference in KOOS QoL subscore in the AM group compared to the AD group is the primary aim. No interim analysis is planned.

Clinical parameters, questionnaires and radiologic modalities will be used as secondary endpoints at predefined times at 3 months (±2 weeks), 6 months (±4 weeks), 12 months (±6 weeks) and 24 months (±8 weeks). They include range of motion (ROM) measured with a goniometer, visual analogue scale (VAS), all KOOS subscores except knee-related QoL, Tegner score, Lysholm score and EQ-5D. The difference between the two treatment groups and within the group will be the secondary aims. Information about work (return to work), physical activity and return to sport will also be collected.

Additionally, at the follow up after 24 months, a hop test validated by Reid [48], standing radiographs and MRI will be done. All participants will be invited to late follow ups after 5 and 10 years respectively.

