### Sample size

A difference in KOOS QoL subscore of 8–10 has previously been shown to be clinically significant [50, 51]. With 80% power comparing the two treatment groups 24 months after surgery by a two-sample *t*-test, power analyses is therefore based on detecting a difference of 10. Using a standard deviation (SD) of 18 ([37, 50] http://www.koos.nu/koosfaq.html), this yields 52 patients in each group. By adding 10 % due to drop out and loss to follow-up, a total of 114 patients will be included.

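### The analysis section words the primary comparison as KOOS QoL from baseline to 24 months, while the aim, hypotheses and sample size use the 24-month difference; the test and the role of the baseline score should be fixed.

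*Protocol article*

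**What the plan says.** Three sections of the protocol article agree. Endpoints: "At 24 months follow up, the difference in KOOS QoL subscore in the AM group compared to the AD group is the primary aim". Hypothesis: the null is "There is no difference in KOOS QoL following AM or AD treatment of a symptomatic full thickness knee cartilage defect", with the time point given as 24 months after surgery. Sample size: the power calculation is for "comparing the two treatment groups 24 months after surgery by a two-sample" t-test, with a difference of 10, SD 18 and 80% power, giving 52 per group and 114 in total.

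The Statistical analysis section, which says how the primary objective is tested, differs: "The test for the primary objective of comparing KOOS QoL from baseline to 24 months between the groups can be performed". The method it names is a t-test, labelled post hoc. Where this test stands in relation to the model, and what replaces it if normality fails, is put this way: "following the LMM. If the data is not normally distributed, a non-parametric analysis will be done using the Mann-Whitney" test. The model is described as "linear mixed models (LMM), including a random center effect for hospital". On covariates, the section gives as examples of possible confounders "age of the patient and severity of the cartilage lesion, these variables will be included in the LMM". Baseline KOOS QoL is not named. The section does not say whether it enters the model in some other way, for example as a repeated outcome.

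**The concern.** The phrase in the analysis section reads most naturally as a comparison of change from baseline. The other three sections concern the 24-month score. The verb is permissive (the t-test may be done, not will be done), and the text does not say whether the t-test is a contrast from the fitted model or a separate comparison.

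Under randomisation the difference in 24-month means and the difference in mean change have the same expected value, so the treatment effect targeted is the same. In any one data set, however, the two estimates differ by the chance baseline imbalance, and their precision differs by an amount that depends on the correlation between baseline and 24 months. The p-value and confidence interval reported as the trial's result could therefore come from either analysis. The baseline score is often a useful predictor of the later score, so whether it is used also affects precision.

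**Working it through.** **Inputs.** From Sample size: difference 10, SD 18, 80% power, 52 per group. From Statistical analysis: significance level 0.05. From Hypothesis: a non-directional alternative, hence two-sided. Assumed, because the article does not give them: SD 18 is the SD of a single score and is the same at baseline and 24 months; the baseline-to-24-month correlation r ranges from 0.1 to 0.7.

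**Step 1: the plan's own figure.** The normal approximation gives n = 2 × (1.960 + 0.842)² × 18² / 10² = 50.9, so 51 per group. For the t-test, the standard error is 18 × √(2/52) = 3.53, the noncentrality is 10 / 3.53 = 2.83 on 102 degrees of freedom, and power is 80.1%. With 51 per group it is 79.3%. So 52 per group is correct for an unadjusted two-sample t-test at 24 months. Adding 10% gives 104 × 1.10 = 114.4, stated as 114.

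**Step 2: how far the two versions can differ in one data set.** The difference in change equals the 24-month difference minus the baseline difference. With SD 18 at baseline and 52 per group, the baseline difference has standard error 18 × √(2/52) = 3.53 points. A gap of about 3.5 points between the two estimates is thus one standard error of chance imbalance, against a target difference of 10.

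**Step 3: power under each reading, 52 per group.**

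SD of change = 18 × √(2(1 − r)). Baseline-adjusted SD = 18 × √(1 − r²). Each replaces 18 in Step 1.

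| r (assumed) | SD of change | Power, raw change | Adjusted SD | Power, baseline-adjusted | Power, unadjusted 24-month |
|---|---|---|---|---|---|
| 0.1 | 24.1 | 55% | 17.9 | 81% | 80% |
| 0.3 | 21.3 | 66% | 17.2 | 84% | 80% |
| 0.5 | 18.0 | 80% | 15.6 | 90% | 80% |
| 0.7 | 13.9 | 95% | 12.9 | 98% | 80% |

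Taking 51 completers per group (90% of 57) instead lowers each power figure by less than 1 percentage point.

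**Step 4: ordering.** 2(1 − r) − (1 − r²) = (1 − r)², which is never negative, and 1 − r² is never above 1. So in this calculation the adjusted comparison is never less precise than the change score or the unadjusted score. The raw change score is less precise than the unadjusted score when r is below 0.5 and more precise when r is above 0.5.

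**Step 5: dependence on what SD 18 is.** If 18 is already the SD of the change, the 80.1% in Step 1 belongs to the change-score test and there is no shortfall. The Sample size section does not say which it is.

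**The case against.** The strongest reply is that a single loose phrase is being set against three clear statements, and that most of what follows from it depends on reading it unfavourably. Much of this stands.

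- **Power.** A reader might infer that the stated 80% is wrong, or does not apply to the planned test. The documents do not support that. The figure reproduces for the test named in the Sample size section. A shortfall needs three things together: SD 18 as a single-score SD, a raw change-score test, and a correlation below about 0.5. The article settles none of them.
- **The t-test.** A reader might infer that it discards the hospital effect and the covariates. Since it follows the model, it may well be a t-test of a model contrast, which keeps both. In this setting, post hoc need not mean unplanned.
- **The covariates.** The list is introduced as examples, so it is open. A longitudinal model could also use the baseline score as an outcome without listing it as a covariate. It can be said that baseline is not named, but not that it is excluded. Full model specification may also stand in an analysis plan that is not shown.
- **Earlier visits.** The phrase "all KOOS subscores except knee-related QoL" might be taken to mean that KOOS QoL is not measured at 3, 6 and 12 months. It sits in the list of secondary endpoints, where QoL is excepted because it is the primary endpoint. It says nothing about whether QoL is collected at those visits.

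What the reply does not remove is the difference in wording itself. It lies within the article, in the one sentence that says how the primary objective is tested, and that sentence is permissive about the test.

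**Conclusion.** The concern holds as a matter of inconsistent and loose wording of the primary analysis, together with a precision gain that is available at no cost. The sample size is not in error, and no increase follows from the documents.

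The size is conditional. With SD 18 for a single score at both times and 52 per group, a raw change-score test would have about 55% to 66% power at correlations of 0.1 to 0.3, would match the planned 80% at 0.5, and would reach 95% at 0.7. Adjusting the 24-month comparison for baseline gives 81% to 98% over the same range. The correlation range is an assumption throughout. The case for baseline adjustment does not depend on knowing it, because adjustment does at least as well as either alternative at every value.

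**What to change.** In the Statistical analysis section, name one primary estimate: the AM minus AD difference in mean KOOS QoL at 24 months. Take it as the treatment contrast at 24 months from the linear mixed model, with baseline KOOS QoL added to age and lesion severity as fixed covariates and hospital as the random effect, and report its 95% confidence interval and p-value. Let this replace both the baseline-to-24-months wording and the optional post hoc t-test.

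In the Sample size section, state that SD 18 is the SD of the 24-month score, if that is so. The 52 per group can then stand as the size for an unadjusted comparison, which is slightly conservative for the adjusted one.

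The cost is a few sentences in the protocol or analysis plan, best settled before treatment codes are linked to outcomes. The total stays at 114. The baseline score is needed for any baseline-to-24-month comparison, so no new measurement is implied.

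### A loosely defined normality test decides whether the primary KOOS QoL comparison is the mixed model or a Mann-Whitney test that drops the planned adjustment and gives no difference in KOOS points

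*Protocol article*

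**What the plan says.** All of the following is in the protocol article.

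- **Preliminary test** (Statistical analysis): "The normal distribution of the variables will be tested".
- **First branch** (Statistical analysis): "Given normal distribution, the statistical analysis will be performed using linear mixed models (LMM), including a random center effect for hospital". Within it, a t-test is named as an option: "The test for the primary objective of comparing KOOS QoL from baseline to 24 months between the groups can be performed as a post hoc". The covariates belong to this branch only: "To adjust for possible confounders such as age of the patient and severity of the cartilage lesion, these variables will be included in the LMM".
- **Second branch** (Statistical analysis): "If the data is not normally distributed, a non-parametric analysis will be done using the Mann-Whitney" U-test. No estimate, stratification or adjustment is attached to it.
- **Primary aim** (Endpoints): "At 24 months follow up, the difference in KOOS QoL subscore in the AM group compared to the AD group is the primary aim".
- **Sample size** (Sample size): "power analyses is therefore based on detecting a difference of 10", by a two-sample t-test with SD 18, 52 per group and 114 in total.

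Nothing exempts the primary endpoint from the switch.

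**The concern.** The trial has one primary comparison, and the plan does not say which analysis delivers it until the outcome data have been inspected. There are four difficulties.

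1. **The tested quantity is wrong.** A linear mixed model relies on approximately normal residuals and random effects. Raw scores can fail a normality test simply because two arms with different means have been pooled.
2. **The trigger is undefined.** The variable could be the raw score, the change from baseline or a residual; it could be taken at any visit, pooled or by arm; and the test and its threshold are open. Two analysts following the same text could reach different primary analyses.
3. **The planned adjustment is lost.** A standard Mann-Whitney test takes one value per patient and has no place for the hospital effect (the trial names seven hospitals), age or lesion severity.
4. **The result is on another scale.** The sample size rests on a difference in KOOS points. A Mann-Whitney test alone gives a p-value about rank ordering, which cannot be compared with 10 points.

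At stake are the pre-specification and interpretability of the primary result.

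**Working it through.** **Step 1: reproduce the plan's figure.** Inputs from Sample size, Hypothesis and Statistical analysis: difference 10, SD 18, power 80%, two-sided alpha 0.05, allocation 1:1.

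- Normal approximation: n per arm = 2(1.960 + 0.842)² × (18/10)² = 2 × 7.85 × 3.24 = 50.9, so 51.
- Two-sample t-test (noncentral t): 51.84, so 52 per arm, with power 80.1% at 52.
- Total: 104 × 1.10 = 114.4, stated as 114.

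The stated 52 and 114 are reproduced. After 10% loss, 114 × 0.90 / 2 = 51.3 per arm remain; t-test power at 51 is 79.3%.

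**Step 2: like-for-like cost of the fallback under normality.** The asymptotic efficiency of Mann-Whitney relative to the t-test is 3/π = 0.955.

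- Effective size at 52 per arm: 52 × 0.955 = 49.7, giving power 78.3%.
- Size needed for 80%: 51.84 / 0.955 = 54.3, so 55 per arm.

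The loss is 80.1 − 78.3 = 1.8 points.

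**Step 3: how often the switch would occur.** The documents give no score step, mean or named test, so these are assumptions: normal latent scores with SD 18, rounded to 6.25-point steps and clipped to 0–100, a true difference of 10, 52 per arm, Shapiro-Wilk at 0.05, and 3000 simulated trials per row.

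| Mean of lower arm | Switch, pooled raw scores | Switch, within-arm residuals | Power, t-test | Power, Mann-Whitney |
|---|---|---|---|---|
| 50 | 28% | 13% | 82% | 79% |
| 60 | 63% | 23% | 78% | 76% |
| 70 | 100% | 78% | 80% | 78% |

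Moving from raw scores to residuals changes the switching rate from 63% to 23% in the middle row. With SD 22 the rates are 27%, 91% and 100% on raw scores and 11%, 43% and 96% on residuals.

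**Step 4: type I error.** In the SD 18 runs with no true difference, the t-test rejected in 4.9% to 5.2% of trials, Mann-Whitney in 4.6% to 4.7%, and the two-stage rule in 4.6% to 4.8%. The linear comparison keeps its level on these coarse scores, so the preliminary test protects against nothing here.

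**Step 5: what each branch delivers, from the text.**

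| Feature | Mixed model | Mann-Whitney |
|---|---|---|
| Hospital effect | yes, random | none |
| Age and lesion severity | yes | none |
| Difference in KOOS points | yes | none planned |

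**The case against.** The strongest defence is that both branches and the trigger were written in advance, so this is not free selection after the fact. The article is also a condensed account: tested may include graphical checks, and variables may be loose wording for residuals. An analysis plan could name the test and add a point estimate, such as Hodges-Lehmann, beside the rank test. The error rate holds, the sample size is untouched, and the matched power loss is about 2 points. Under real skew the rank test can win. With gamma-distributed scores (an assumption), a 10-point shift, SD 18 and 51 per arm, power is 78% for the t-test against 84% for Mann-Whitney at shape 4, and 80% against 90% at shape 2.

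Most of this stands and limits the severity. It does not remove the point, because the article states the switch as a rule and an analysis plan that follows it inherits the problem.

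A reader might also infer more than the document supports:

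- **A large power loss.** A baseline-adjusted linear model would reach about 84% to 94% at 52 per arm for baseline correlations of 0.3 to 0.6. But the plan names only age and lesion severity as examples of covariates, not baseline KOOS QoL. That gain is a separate benefit and depends on an assumed correlation. The ranked variable might also be change from baseline, since the section words the objective that way.
- **Loss of repeated visits and a completers-only analysis.** The only random effect named is hospital, the visit schedule is listed for the secondary endpoints, and missing-data handling may sit in the analysis plan. Both losses are inferred, not stated.
- **A changed hypothesis.** The Hypothesis section speaks of a difference in KOOS QoL without saying mean difference, so a rank test is compatible with it. The firm point is narrower: the 10-point target needs an estimate in KOOS points.

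**Conclusion.** The point holds as a weakness in pre-specification, adjustment and interpretability, not as a failure of validity. A preliminary test that is undefined, and as worded looks at the wrong quantity, selects the primary analysis. If it fails, the primary test loses the hospital effect and the planned covariates and yields nothing on the KOOS scale.

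The switch is far from remote: about 28% to 100% on pooled raw scores and 13% to 78% on residuals. Those rates rest on the assumed 6.25-point steps, SD 18, lower-arm means of 50 to 70 and Shapiro-Wilk at 0.05. The article would not support a claim of type I error inflation. The power cost, about 2 points under normality, is small and can change sign. The severity is therefore that it should be fixed, not that the trial cannot proceed without it.

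**What to change.** Before treatment-group outcomes are examined, amend the Statistical analysis section or the analysis plan as follows.

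1. Remove the normality test as a condition for choosing the method.
2. Make the linear mixed model with a random hospital effect, age and lesion severity the primary analysis whatever the distribution. Report the 24-month difference in KOOS QoL with its confidence interval.
3. Check residuals. If they are poor, report robust (sandwich) or bootstrap intervals for the same difference.
4. Keep Mann-Whitney as a labelled sensitivity analysis.
5. Apply the same rule to the continuous secondary endpoints.

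Whether to add baseline KOOS QoL to the model is a separate decision.

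The cost is a few sentences and one extra sensitivity run, with possibly slightly less power than a rank test if the scores are strongly skewed. The sample size stays at 52 per arm and 114 in total, and no new data are needed.

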### Demographics

Age, gender, nationality, social status, work status, use of medication, prior medical history height in cm, weight in kg, Body Mass Index (BMI) and injury mechanism (if any) are collected at inclusion.

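### Plain chi-squared tests for the categorical secondary outcomes are valid but leave out category order, hospital, age, lesion severity and baseline work status, at some cost in power

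*Protocol article*

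**What the plan says.** All references are to the protocol article, Methods and design.

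- **Statistical analysis, categorical outcomes:** "To evaluate the efficacy of treatment in terms of categorical outcome measures we plan to use Chi-squared tests". No ordinal, stratified or adjusted version is named.
- **Statistical analysis, other outcomes:** given normality, the plan is "linear mixed models (LMM), including a random center effect for hospital". The covariates are placed in the same model: "To adjust for possible confounders such as age of the patient and severity of the cartilage lesion, these variables will be included in the LMM". The fallback is a rank test: "If the data is not normally distributed, a non-parametric analysis will be done using the Mann-Whitney" U-test. The significance threshold is p "< 0,05 is considered statistically significant".
- **Endpoints:** the listed secondary measures include "visual analogue scale (VAS), all KOOS subscores except knee-related QoL, Tegner score, Lysholm score and EQ-5D", with range of motion and, at 24 months, a hop test, radiographs and MRI. The section adds: "Information about work (return to work), physical activity and return to sport will also be collected".
- **Demographics:** the items collected at inclusion begin "Age, gender, nationality, social status, work status, use of medication".

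The article does not say which outcomes count as categorical, and it does not define return to work or the categories of work status.

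**The concern.** The investigators considered hospital, age and lesion severity important enough to build into the model for the numeric outcomes. The test fixed for the categorical outcomes can use none of them. This is a stated choice of method, not a detail left open: an analysis plan would have to depart from the sentence to do better.

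Two kinds of information are lost. If an outcome has ordered categories, Pearson's chi-squared spends k − 1 degrees of freedom on any pattern of difference, whereas a treatment is most likely to shift patients up or down the scale. If an outcome is binary, there is no order to lose, but a prognostic baseline variable that has been recorded goes unused. Return to work is the clearest case. Work status at inclusion is likely to predict it and is already on the case report form, but the plan does not connect the two.

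At stake is the precision of secondary results on work, sport and activity. The Background stresses the occupational burden of these disorders, so they bear on the trial's rationale.

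**Working it through.** **1. The trial's own sample size.** Inputs from the Sample size section: difference 10, SD 18, power 80%, two-sample t-test. Two-sided 0.05 is taken from the stated threshold and the non-directional alternative hypothesis.

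- Normal approximation: n = 2 × (1.96 + 0.842)² × 18² / 10² = 50.9, so 51 per arm.
- t-test: 51.84, so 52 per arm, with power 80.1%. This matches the stated 52.
- Drop-out: 104 × 1.10 = 114.4, stated as 114.

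The point does not touch this calculation. It supplies the 52 per arm used below.

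**2. Ordered categories.** Assumptions (none is in the article): k equally likely levels in one arm, and the other arm shifted by a common odds ratio. Example for k = 3 and odds ratio 2: the cumulative odds 0.5 and 2 become 0.25 and 1. The cumulative probabilities are then 0.20 and 0.50, and the shifted arm is 20%, 30% and 50% against one third each. Each scenario was simulated 4,000 times at two-sided 0.05. The comparator is the Mann-Whitney test, used as a close stand-in for the proportional-odds test.

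Power of chi-squared vs order-using test (difference in points, taken before rounding):

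| Levels | OR 2.0 | OR 2.5 | OR 3.0 |
|---|---|---|---|
| 3 | 37% vs 47% (10) | 59% vs 70% (11) | 76% vs 84% (8) |
| 4 | 33% vs 49% (16) | 56% vs 73% (18) | 73% vs 86% (13) |
| 5 | 30% vs 49% (18) | 50% vs 74% (23) | 70% vs 88% (18) |
| 6 | 30% vs 51% (21) | 47% vs 73% (26) | 65% vs 88% (23) |

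Analytic check of the first cell: the noncentrality is n × Σ(p₁ − p₂)²/(p₁ + p₂) = 52 × (0.0333 + 0.0018 + 0.0333) = 3.56 on 2 degrees of freedom. That gives power of 37%, as simulated.

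**3. Binary outcome with one baseline covariate.** Assumptions: 52 per arm, 60% response in the control arm, a binary covariate present in half the patients, a treatment odds ratio of 3 within covariate levels, and 1,500 runs. Chi-squared is compared with logistic regression on treatment and the covariate.

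| Covariate log odds ratio | Chi-squared | Adjusted | Difference (points) |
|---|---|---|---|
| 0 | 69.2% | 69.8% | 0.6 |
| 1 | 65.9% | 68.1% | 2.3 |
| 2 | 57.3% | 65.5% | 8.3 |
| 3 | 42.5% | 55.5% | 13.1 |

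The comparison is within rows. The treatment effect is fixed conditionally on the covariate, so the unadjusted effect shrinks down the table.

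**4. Validity.** With no treatment effect, rejection rates were 4.2% to 5.9% across all tests, so chi-squared does not inflate the type I error.

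**5. Size of the trial.** A plain comparison of 60% with 80% at 52 per arm has power of 61%. For binary outcomes, sample size is a larger limit than a weak covariate left out.

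**The case against.** The case on the other side is substantial.

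- **No ordered categorical endpoint is named.** Tegner is listed as a score beside Lysholm, KOOS and EQ-5D, so the plan would send it to the LMM or, if non-normal, to the Mann-Whitney test, which uses order. For imaging the article says only that radiographs and MRI will be done; it gives no grading scale. This stands. A reader might infer that real effects on many-level activity scales or structural grades will be missed through sparse cross-tabulations. The article does not say such scales will be cross-tabulated. The ordinal figures are therefore conditional: they apply to any outcome that is analysed in a few ordered categories.
- **The test is valid, and the gain from adjustment may be small.** Both parts stand. Hospital, age and lesion severity were not themselves simulated; one binary covariate stood in for them, and its effect on power ran from negligible to moderate. The article describes no stratification of randomisation by hospital that the test would have to reflect.
- **Return to work has no definition, denominator or time point here.** This stands, and such detail may sit in a fuller document. A reader might infer that patients not working at inclusion cannot return, and that the analysis should be restricted to those working. The article does not support this. Work status has no defined categories, and a patient on sick leave for the knee may be recorded as not working yet is exactly someone who can return. Power figures for an analysis that codes all such patients as failures would rest on a rule and on rates that the article does not contain.
- **Naming a test does not rule out reporting effect sizes.** This also stands. The lack of a stated interval is not itself an error.

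What remains is that the article fixes an unadjusted, order-blind test for the whole class of categorical outcomes, with the means of improving on it already collected.

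**Conclusion.** The point holds as one of efficiency in secondary outcomes. Under the assumptions shown, ignoring order costs about 8 to 26 points of power for an outcome in 3 to 6 ordered categories. Omitting a baseline covariate from a binary comparison costs about 0 to 2 points if it is weakly prognostic and about 8 to 13 if very strongly so. These sizes rest on assumed category structures, odds ratios, response rates and covariate strength; from the article come only the 52 per arm and the 0.05 threshold.

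No error in the primary analysis or sample size follows, nor does a general claim that real effects will be easily missed. The recommendation is worth making because it is cheap and carries the covariates the investigators already chose for the LMM over to the categorical outcomes.

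**What to change.** Replace the chi-squared sentence, before unblinding, with wording to this effect:

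- **Binary outcomes:** logistic regression adjusted for hospital (as a random effect, in line with the LMM), age, lesion severity and the baseline category where collected.
- **Any ordered outcomes:** proportional-odds regression with the same terms. If cells are too sparse for a stable fit, use a rank test stratified by hospital.
- **Unordered outcomes:** chi-squared may stay.
- **Reporting:** an odds ratio or risk difference with its 95% confidence interval for binary outcomes, and a common odds ratio with its interval for ordered ones.
- **Return to work:** enter the recorded baseline work status as a covariate. Do not exclude everyone not working at inclusion.

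The cost is a change of wording and slightly more analysis work, with no new data, visits or patients; SPSS and R, already named, suffice. The downsides are a proportional-odds assumption to check and possible sparse cells: 104 patients over the seven hospitals listed is about 15 per hospital (104 / 7 = 14.9). The stratified rank test would not carry age, lesion severity or the baseline category.
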